#### Secondary outcomes

The secondary outcomes are measured as described below.Short-form McGill Pain Questionnaire (SF-MPQ): This questionnaire comprises Pain Rating Index (PRI), Present Pain Intensity (PPI), and VAS items. The PRI includes sensory and affective parts with negative, mild, moderate, and severe pain (from 0 to 3) representing the degree, while the PPI values from 0 to 5 represent different degrees of pain. A VAS number of 0 represents no pain, and 10 represents unbearable pain [27].Northwick Park Neck Pain Questionnaire (NPQ): The NPQ has been commonly used in clinical research and has shown high validity and practicability for neck pain assessment [28]. It consists of nine items involving the degree and duration of pain, numbness of upper extremities, sleep, and social activities as well as other quality of life characteristics. The total score is 100, and high scores mean severe disability from neck pain.Range of Motion (ROM) of the neck: This reliable and valid tool, consisting of two gravity goniometers and a compass goniometer, is used to assess the degree of cervical spine movement involving the cervical movement distance of bilateral rotation and flexion without undergoing pain [29]. This measurement is performed by a specific senior researcher, and the mean values will be recorded to facilitate the analysis.Short-form 36-item Health Survey (SF-36): The health-related quality of life and correlation factors including physical function and daily functioning are evaluated by a 5-point scale [30].Self-Rating Anxiety Scale (SAS) and Self-Rating Depression Scale (SDS): The SAS is a relatively simple clinical tool to analyze the subjective symptoms of patients. It is applicable to adults with anxiety symptoms and has a wide range of applications. The SDS can fairly directly reflect the subjective feelings of patients with depression and their changes in treatment. It is mainly applicable to adults with depressive symptoms. Compared to the SDS, the SAS can better reflect the subjective feelings of patients with anxiety tendencies [31].

### Data collecting and monitoring

Data will be recorded in electronic case report forms (eCRFs) by specific outcome assessors, and will be established and monitored by the Data Monitoring Committee (DMC) of the First Affiliated Hospital of Yunnan University of Chinese Medicine. Inspectors will inspect the data, check the study protocol compliance and nonscheduled informed consent documents, and evaluate the conditions of participant recruitment and data quality of this trial. During the evaluation process, the researchers, including acupuncturists and statisticians, will have no eligibility to see the data. Any amendments to this study protocol should be tracked and dated for submittal of a new version to the committee.

According to the data-sharing policy of the Chinese Clinical Trial Registry (CHICTR), data will be transmitted to the official website of Yunnan University of Chinese Medicine (www.ynutcm.edu.cn) within 6 months after this trial is completed. Data will be opened on the condition of publication of the main study findings. In order to protect the participants’ confidentiality, all of the external investigators should be asked to sign the agreement. Any adverse events (AEs) or accidents will be observed, reported, and monitored in time until they are resolved. The safety of the trial will be assessed before and after the treatment to avoid AEs, and a strict investigation and relative follow-up monitoring will be performed if they occur.

### Adverse events

Any possible AEs related to acupuncture intervention that occur, including nausea, fainting, subcutaneous hemorrhage, local infection, stuck needles, or needle breakage will be checked and treated. Details of AEs will be recorded in the CRF by the acupuncturist and security administrator. Severe AEs will be reported to the Ethics Committee and DMC, and compensation will be considered if necessary. Patients who are unwilling to persist with the treatment will be removed from the trial.

### Statistical analysis

All of the data will be entered in the CRFs and input into the database by two independent researchers, calculated by means of the SPSS 25.0 software package. Data analysis and comparison will be performed based on the intention-to-treat (ITT) population and the per protocol (PP) population, contributing to the integrity and objectivity of this study. The ITT population consists of all participants who have been randomized and received at least one session of acupuncture after the baseline. PP refers to the patients who have completed the study and did not violate the protocol. A two-sided value of *P* < 0.05 will be defined as the statistical significance, categorical variables in two groups will be analyzed by chi-squared or Fisher’s exact test, normally distributed data will be analyzed by Student’s *t* test, and non-normally distributed data by the Mann-Whitney *U* test. Continuous variables in two groups including primary outcomes (the PainVision and SEMG parameters) and secondary outcomes will be compared using a general linear model with repeated measurement methods at all time points.

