#### Dropout criteria

Patients who are unable to comply with this study and fail to achieve the expected efficacy, or who experience severe changes in their condition during treatment, will be dropped from the study.

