### Randomization, allocation concealment, and blinding

The eligible patients who meet the criteria will be randomly distributed to the *jin* acupuncture group and the pseudo acupuncture group with an allocation proportion of 1:1. A statistician who is not taking part in the clinical intervention will use SPSS 25.0 (IBM, Chicago, IL, USA) to generate a random allocation sequence. All of the random code information will be stored in sealed opaque envelopes by a well-trained specified assistant, who will randomize and inform the acupuncturists of the treatment assignments by phone. The allocation concealment procedure will not be exposed until the clinical trial is finished completely. Assessments and measurements of the participants will be carried out before and after the treatments and also at the follow-ups by different individuals of the research team. Researcher A will be responsible for the baseline assessment, administration of the questionnaire, and the measurement of cervical range of motion. Researcher B will be in charge of detecting the SEMG signal on the cervical extensor muscles. Researcher C will detect and record the pain degree (PD) and pain rate (PR) with the PainVision analyzer. Researcher D will be responsible for the analysis of SEMG data. A licensed acupuncturist who has worked for more than 18 years will perform acupuncture interventions on the patients, and patients will be treated in a shielded clinic room and deprived from knowing something about the pattern of treatment.

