### Outcome measures

#### Primary outcome measures

The following primary outcome measures will be used to evaluate the effectiveness at weeks 4, 8, and 16 after randomization, respectively, compared with the baseline.Pain degree (PD) and pain rate (PR): With a measurement accuracy of 0.1 μA, 0.3 ms pulse width, and 50 Hz pulse frequency, both indicators will be calculated using the current perception threshold (CPT) and pain equivalent current (PEC) with the PainVision analyzer according to the following formula [24, 25]:$$ PD=\frac{PEC- CPT}{CPT}\times 100\kern0.5em PR=\frac{PEC}{CPT} $$Surface electromyography (SEMG): With the patient in a prone position, a sticker will be placed on the affected side cervical extensor muscles (2 cm lateral to the posterior midline of the neck). The SEMG signal will be detected through an eight-channel module ME6000 biomonitor (Mega Electronics Ltd., Kuopio, Finland) as the operator successively applies 25% (maximum voluntary contraction, MCV), 50% MCV, and 100% MCV resistance, respectively, to the posterior occipital area. The system will automatically record and transmit the signal to generate the original image, and indicators of muscle fatigue including median frequency (MF), mean power frequency (MPF), average rectified value (ARV), and root mean square (RMS) will be calculated by Mega Win software for statistical analysis [26].

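### The set labelled ITT is a modified ITT set, and the named repeated-measures model would narrow it to treated patients with every visit unless missing visits are handled first

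*Protocol article*

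**What the plan says.** All references are to the protocol article.

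- **ITT set** (Statistical analysis): "The ITT population consists of all participants who have been randomized and received at least one session of acupuncture after the baseline".
- **PP set** (Statistical analysis): "PP refers to the patients who have completed the study and did not violate the protocol".
- **Model** (Statistical analysis): continuous primary and secondary outcomes "will be compared using a general linear model with repeated measurement methods at all time points", with the data "calculated by means of the SPSS 25.0 software package". The section also lists Student's t test and the Mann-Whitney U test, without saying at which visits or for which outcomes they apply.
- **Visits** (Primary outcome measures): the measures are used to "evaluate the effectiveness at weeks 4, 8, and 16 after randomization, respectively, compared with the baseline".
- **Removal of patients**: under Dropout criteria, patients who cannot comply and "fail to achieve the expected efficacy, or who experience severe changes in their condition during treatment, will be dropped from the study". Under Adverse events: "Patients who are unwilling to persist with the treatment will be removed from the trial". Neither section says whether these patients are still assessed.
- **Who knows the arm** (Randomization, allocation concealment, and blinding): an assistant holds the codes, "who will randomize and inform the acupuncturists of the treatment assignments by phone".

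The article says neither that incomplete cases are deleted nor that missing values are imputed. Such rules may sit in an analysis plan that is not shown, and their absence is not the point here. The point concerns what the article does fix: the definition of the set and the choice of model.

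**The concern.** An ITT set earns its name by keeping every randomised patient in the assigned arm. Here membership depends on something that happens after randomisation, namely whether a session is given. The set is a modified ITT set, and the balance that randomisation provides is no longer fully guaranteed.

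The model can narrow the set a second time. The classical repeated-measures general linear model treats the visits as one multivariate response and needs all of them. A patient seen at weeks 4 and 8 but not at week 16 then contributes nothing to it.

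The ITT analysis is presented beside a PP analysis as a check on robustness. If both rest largely on patients who were treated and fully observed, agreement between them says less than it appears to. The removal rules add to this: if patients leave because of how they are faring, the complete cases are a selected group, and the selection may differ between arms.

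**Working it through.** **Step 1. Compare the sets.**

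| Set | Randomised | Treated at least once | Every visit present | No protocol violation |
|---|---|---|---|---|
| True ITT | required | – | – | – |
| ITT as defined | required | required | – | – |
| ITT as defined, classical repeated-measures GLM, no prior handling of missing visits | required | required | required | – |
| PP | required | implied | implied by completing the study | required |

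The second row follows from the text. The third follows from the named model, on the stated condition. It differs from PP mainly in keeping protocol violators who attended every visit.

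**Step 2. Size at the protocol's own loss rate.** The inputs are 166 patients, 83 per arm, and 10% loss (Study population and sample size).

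- Patients leaving the model: 0.10 × 166 = 16.6, about 17.
- Patients remaining: 166 − 16.6 = 149.4, or 74.7 per arm.

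**Step 3. Effect on power, for illustration.** The protocol's inputs are a VAS difference of 2, SD 5 and two-sided alpha 0.05. VAS is a secondary outcome in this protocol, so the result is only indicative for the primary ones.

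Reproducing the stated size first: n per arm = 2 × (1.960 + 1.645)² × 5² / 2² ≈ 162.4, so 163. After 10% loss this is 163 / 0.9 = 181.1, so 182 per arm against the stated 83. The stated 166 does not reproduce. That is a separate matter and is not relied on here.

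Power for n per arm ≈ Φ(2 / (5 × √(2/n)) − 1.960):

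- n = 83: Φ(2.577 − 1.960) = 0.73.
- n = 74.7: Φ(2.445 − 1.960) = 0.69.

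**Step 4. Larger figures need an assumption.** If each of the three follow-up visits were missed independently with probability p, the share with at least one gap would be 1 − (1 − p)³.

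| p (assumed) | Share incomplete | Of 166 |
|---|---|---|
| 3% | 0.087 | about 14 |
| 5% | 0.143 | about 24 |
| 10% | 0.271 | about 45 |

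Only the first row lies within the protocol's 10% allowance. The article gives no per-visit rate, and its own routes of loss (dropping and removal) suggest patients leaving for good more than scattered misses.

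**Step 5. What cannot be sized.** The article gives no rate of patients who are randomised but never treated, and no split of losses by arm or reason. Neither the effect of the ITT definition nor any bias from informative loss can be calculated from it.

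**The case against.** The strongest reply is that the article never says incomplete patients are deleted. It names no specific SPSS procedure, and imputation or a mixed model may be intended in a document not shown. This stands. A reader might infer that the ITT result simply is an analysis of treated completers, but the text supports that only on the condition that missing visits are not handled first.

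Three further readings are tempting and go too far.

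- *Never-treated patients are excluded by someone who knows the arm.* The acupuncturist does know it, but the article gives the acupuncturist no part in deciding who starts. Patients are blinded, and both arms have the same number of sessions. The exclusion rests on whether a session took place, not on an unblinded judgement. Comparability is not fully guaranteed; it is not shown to be lost.
- *ITT and PP will agree only because both are completer analyses.* PP also removes protocol violators. With 12 sessions in 4 weeks, a patient could breach the protocol and still attend every assessment, so the two sets can differ.
- *Week-4 data are thrown away whenever week 16 is missed.* This would be true of the classical model. However, the t test and Mann-Whitney U test are also listed, and a single-visit test would use everyone seen at that visit.

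A fair point about the remedy also stands: no model recovers visits that were never made, and a never-treated patient with only a baseline value adds almost nothing. Relabelling the set helps little without follow-up.

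None of this removes the mislabelled definition, which is explicit, or the choice of a model that, as classically run, needs complete cases.

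**Conclusion.** The concern holds in two parts of different strength. First, the set labelled ITT is a modified ITT set. This is explicit in the text; the number of patients affected is unknown and may be small. Second, the named model would turn the ITT analysis into a complete-case analysis of treated patients, closer to PP, unless missing visits are handled beforehand. This rests on how the classical SPSS procedure works and on that condition.

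At the protocol's own 10% loss, about 17 of 166 patients would leave the model, with power on the protocol's VAS inputs moving from about 0.73 to 0.69. Figures of 24 or 45 patients depend on assumed independent misses beyond that allowance and should not be quoted as expected.

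The modest loss of power matters less than possible bias. The removal rules depend partly on the course after randomisation, so missing data may be informative, but the article gives nothing from which to size this. The change is worth making, and is cheap.

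**What to change.** 1. Define ITT as all randomised patients, analysed in their assigned arm.
2. Replace the repeated-measures GLM with a linear mixed model (MIXED in the same SPSS package), which uses every observed visit and is valid under missing at random. Because that assumption may fail here, add a sensitivity analysis to departures from it.
3. Keep the set defined by treatment received as a sensitivity analysis, labelled modified ITT.
4. State that outcome assessments at weeks 4, 8 and 16 continue for patients who stop treatment, where they agree. This concerns data collection only; it takes no position on when treatment should stop.

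The cost is a few sentences in the Statistical analysis section, a different procedure in the same software, slightly more analysis work, and some effort to see patients who have stopped treatment. The effect may be slightly diluted if some patients are never treated. No extra patients are needed. The article describes the trial as ongoing, so the change belongs before any comparison of the arms.

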**Design:**

This is a parallel-design, two-arm, patient-assessor blinded, randomized, sham-controlled clinical trial. A total of 166 patients with CEH aged from 18 to 70 will be recruited and assigned randomly into a *jin* acupuncture group and a pseudo acupuncture group at a 1:1 ratio; they will receive 12 sessions of real acupuncture and sham acupuncture for 4 weeks, respectively, during the study. The primary outcomes are pain degree (PD) and pain rate (PR) calculated by the PainVision analyzer, as well as parameters detected by surface electromyography (SEMG). The secondary outcomes will be measured with the short-form McGill Pain Questionnaire (SF-MPQ), range of motion (ROM) of the neck, the Northwick Park Neck Pain Questionnaire (NPQ), the 36-item short-form Health Survey (SF-36), the Self-Rating Anxiety Scale (SAS), and the Self-Rating Depression Scale (SDS). Clinical assessments will be evaluated at baseline and in the fourth week as well as in the eighth and sixteenth weeks. Adverse events will be noted and recorded for the safety evaluation.

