### Participants

#### Study population and sample size

Patients with CEH meeting the diagnosis of the International Classification of Headache Disorders, 3rd edition (ICHD-3) formulated by the IHS [5] will be enrolled. The reduction of the visual analog scale (VAS) average score was 6.37 to 2.31 after triple acupuncture treatment compared to 6.37 to 2.52 for conventional acupuncture treatment according to a relevant study [23]. We propose to set the VAS of the short-form McGill Pain Questionnaire (SF-MPQ) average score as 2 and 4 for the *jin* acupuncture group and pseudo acupuncture group, respectively. Given a significance level of 0.05, a standard deviation of 5, and power of test of 0.95, and considering a 10% loss rate, 166 participants in total are needed with 83 in each group.

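### The repeated-measures model most literally treats baseline as an outcome level and states no baseline adjustment; modelling the three post-treatment visits with baseline as a covariate and one named contrast would be a free gain in precision

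*Protocol article*

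**What the plan says.** The Protocol article, Statistical analysis, gives one model for the PainVision and SEMG primary outcomes and for the secondary outcomes: they "will be compared using a general linear model with repeated measurement methods at all time points". The threshold is two-sided: "A two-sided value of *P* < 0.05 will be defined as the statistical significance".

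The Abstract (Design) lists the visits: "Clinical assessments will be evaluated at baseline and in the fourth week as well as in the eighth and sixteenth weeks". The Interventions section gives the same schedule: one evaluation before treatment, one after the 4 weeks of treatment, and follow-up at weeks 8 and 16.

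The Primary outcome measures section says that the primary measures "will be used to evaluate the effectiveness at weeks 4, 8, and 16 after randomization, respectively, compared with the baseline".

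The article does not call baseline a level of the time factor. It does not say whether the group effect or the group-by-time interaction is the test, and it mentions no baseline covariate.

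**The concern.** Randomisation makes the expected arm difference at baseline zero. If that visit is one of four levels of the outcome, the group main effect averages a zero with three treatment effects and understates the post-treatment difference. The group-by-time interaction avoids this dilution, but it spreads a single question over 3 degrees of freedom.

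The comparison with baseline in the Primary outcome measures section could also mean change scores, or separate comparisons at each visit. Both are valid under randomisation, but both are less precise than adjusting for baseline as a covariate. Unless its meaning is fixed, the phrase could also be taken as change within an arm.

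At stake is precision that the trial could take from a value already measured on every patient, and a clear statement of which number is the treatment effect.

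**Working it through.** **The plan's own figure.** Study population and sample size sets the VAS "average score as 2 and 4 for the *jin* acupuncture group and pseudo acupuncture group, respectively", a difference of 2. It continues "Given a significance level of 0.05, a standard deviation of 5, and power of test of 0.95, and considering a 10% loss rate", and concludes that "166 participants in total are needed with 83 in each group". For two means, n per arm = 2(1.960 + 1.645)² × 5² / 2² = 162.4, so 163, or 163/0.9 = 181.1, so 182 after 10% loss. The stated 83 per arm is not reproduced. With 75 per arm and SD 5, the power of a simple two-group comparison is about 68 to 69%. With 75 per arm, 95% power would need an SD of about 3.4. The power figures below are therefore illustrations and do not check a planned power.

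**Inputs.**
- n = 75 per arm: 83 × 0.9 = 74.7, with allocation 1:1.
- Standardised effect d = 2/5 = 0.4, from the VAS. The VAS belongs to a secondary outcome, not to PainVision or SEMG.
- Two-sided alpha 0.05.
- Assumed, because the article does not give them: the same effect at weeks 4, 8 and 16, and an equal correlation r between any two visits.

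**Dilution.** With arm differences (0, d, d, d), the four-visit main effect has expectation (0 + 3d)/4 = 0.75d, that is 0.30 SD instead of 0.40 SD. The factor 3/4 relative to the mean post-treatment effect holds whatever r is and however the effect changes over visits. It applies to the main effect only.

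**Noncentralities**, with (n/2)d² = 37.5 × 0.16 = 6:
- Group main effect over four visits (1 df): 6 × 0.75² / ((1 + 3r)/4) = 13.5/(1 + 3r).
- Group-by-time (3 df): the squared deviations of (0, d, d, d) from their mean sum to 0.75d², so 6 × 0.75/(1 − r) = 4.5/(1 − r).
- Mean of the three later visits, adjusted for baseline (1 df): 6 / ((1 + 2r)/3 − r²).
- Week 4 only: unadjusted 6; change score 6/(2(1 − r)); baseline-adjusted 6/(1 − r²).

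Power from the noncentral F distribution:

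| Test | r = 0.3 | r = 0.5 | r = 0.7 |
|---|---|---|---|
| Main effect, four visits | 75% | 64% | 55% |
| Group-by-time, 3 df | 55% | 71% | 91% |
| Baseline-adjusted mean of weeks 4, 8, 16 | 95% | 96% | 99% |
| Week 4, unadjusted | 68% | 68% | 68% |
| Week 4, change score | 54% | 68% | 88% |
| Week 4, baseline-adjusted | 72% | 80% | 93% |

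A simulation of 4,000 trials at r = 0.5 gave 64%, 71% and 97% for the first three rows.

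**Sensitivity.**
- At r = 0.8, the interaction has 98.6% power and the adjusted mean 99.9%, a gap of about 1 point. The main effect falls to 51%.
- With SD 3.4 and r = 0.5, the first three rows become 92%, 97% and about 100%.
- If the effect fades (assumed differences 2, 1, 0 at weeks 4, 8, 16) and r = 0.5, the 3-df interaction has 66% and the adjusted post-treatment mean 47%. The adjusted week 4 comparison has 80%.

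**The case against.** The strongest reply is that the article does not say what the concern supposes. Its one sentence does not name baseline as an outcome level, and the Primary outcome measures section lists weeks 4, 8 and 16 as the times at which effectiveness is judged, with baseline as the reference. The words about all time points could mean those three visits. Covariates and the tested term are commonly left to a full protocol or analysis plan that is not shown here. This stands in part. The four-visit reading is the most literal one given the schedule, but it is a reading, and the missing covariate is not an error in itself. What remains is that the article does state a model, and that a better one can be stated with the same data.

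A reader might infer that the reported group effect will be 3/4 of the true difference. The document does not support that. It holds only if the group main effect over four visits is the test, and not for the interaction, for change scores or for comparisons at each visit.

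A reader might also infer that the planned analysis is biased or inflates false positives. Under randomisation, the interaction, change-score and visit-wise comparisons are valid; the issue is efficiency.

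Finally, the size of the loss rests on an assumed correlation, on an effect that persists 12 weeks after treatment ends, and on a VAS effect size that says nothing specific about the primary outcomes. That also stands.

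**Conclusion.** The point holds as a free improvement. Read most literally, the model includes the pre-treatment value as an outcome level, states no baseline adjustment and names no tested contrast. The 3/4 dilution is exact, but it is conditional on the group main effect being the test.

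Under the illustrative assumptions and r from 0.3 to 0.7, the main effect loses about 20 to 45 points of power against the baseline-adjusted post-treatment mean. The 3-df interaction loses about 8 to 41 points, falling to about 1 point at r = 0.8. If the effect fades, the interaction can beat the adjusted mean. At week 4 alone, adjustment adds about 4 to 24 points over the unadjusted comparison. None of these figures is a power statement for PainVision or SEMG, for which the article gives no effect size or SD.

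**What to change.** In Statistical analysis, replace the sentence on the repeated-measures model with wording such as: *Each continuous outcome is analysed by a linear repeated-measures model for weeks 4, 8 and 16, with arm, visit, arm-by-visit, the baseline value and baseline-by-visit as terms. The primary contrast is the baseline-adjusted difference between arms at week 4; the differences at weeks 8 and 16 are supporting.* Week 4, the end of treatment, is an example. The sponsor may choose another visit or the mean of the three visits, but one contrast must be named before the data are unblinded. With the arm-by-visit term in the model, the treatment effect is not defined until that choice is made.

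In Primary outcome measures, state that the comparison with baseline means this baseline-adjusted difference between arms and not a change within an arm.

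The cost is two changes of wording, recorded as a dated amendment. The baseline value is already collected, the planned software can fit the model, and no patient or visit is added.
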